#### Intervention: STEP Care plus standard best practice cancer care

Those patients randomised to the intervention arm will receive STEP Care in addition to standard best practice cancer care. STEP Care consists of, at minimum, monthly palliative care consultations and follow up for at least 3 months (in total, minimum of four consultations—initial consultation plus follow up for 3 months). These consultations will be primarily based in the outpatient setting, unless coinciding with a hospital admission, in which case the consultation can be conducted as an inpatient.

All STEP Care consultations will be conducted by an accredited palliative care physician or specialist nurse. At each consultation, a series of domains will be reviewed and activities undertaken (Table 2). Those areas covered in each consultation will be recorded in a standardised manner using the framework provided by the PC-NAT-PD [39]. All STEP consultations will be audio-recorded to enable content review of services delivered. An audit of 20% of all audio-recorded consultations and associated documentation using the Needs Assessment Tool: Progressive Disease–Cancer (NAT: PD-C) [39] will be undertaken based on consecutive cases.

**Table 2 Tab2:** Key components of STEP Care intervention

1. Identification of patients for eligibility at standardised transitions in the illness course	
2. Initial hospital based palliative care consultation, addressing:	
(a) Review of underlying disease management	
(b) Screening for symptom distress	
(c) Screening for psychological distress	
(d) Review of informal social supports	
(e) Review of formal community supports, including local community palliative care	
(f) Providing information	
(g) Advance care planning discussions	
(h) Involvement of family carer, including enquiry of concerns, needs for information	
3. Regular follow-up, at minimum monthly for minimum of 3 months	
4. Case conference with the general practitioner within 28 days, addressing	
(a) Current and anticipated problems	
(b) Recommended management and therapies	
(c) Designation of responsibility for different aspects of care	

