In addition, demographic, clinical, feasibility and health service data will be collected from patient medical records, Medicare records, nurse-led diaries and qualitative exit interviews with participating clinicians and carers following bereavement (Table 4). Each month, the research nurse will complete a diary involving collection and standardised reporting of assessed performance status, illness understanding and use of health services. Service data prompted for will include hospital stays, use of emergency department, general practitioner visits, community or allied health visits including community palliative care services. Specific details of health service use provided by patients and carers will be confirmed with the administering service where required (Appendix 1).

**Table 4 Tab4:** Measures of study feasibility

Domain	Measure	Unit of measure
Feasibility		
Number of participants	Identified as eligible	Number
	Consented to participate	Percentage
	Completion of study	Percentage
Step care delivery	Number of initial STEP consultations completed within 14 days planned timeframe	Percentage within 14 days
	Number of interactions per patient	Number consultations
	Time from enrolment to first step interaction	Days
	Completion of outcome measures	Percentage of missing data
	Fidelity of step delivery between recording and documented activities using NAT:PD-C [39, 40]	Percentage content correlation within random audit of 20% of consultations
Acceptability of Step Care		
To patients and carers	Number of withdrawals from STEP Care intervention	Percentage
	Number of adverse events arising from STEP Care intervention	Percentage
	Qualitative interviews with STEP Care family carers following bereavement	Qualitative data
Acceptability of Step Care to clinicians		
To clinicians	NAT: PD-C documentation completion rate by participating STEP care physicians	Percentage of content recorded for consultations conducted
	Focus group with STEP Care physicians regarding perspectives on STEP care content, timing and frequency of interaction	Qualitative data

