Satisfaction with care (carer): FAMCARE [51] is a 20-item scale developed to measure family members’ satisfaction with delivery of palliative care.

Patient-reported, cost-utility weights, measured by a cancer specific multi-attribute utility index QLU-C10D [40] is calculated based upon the recordings made by patients on the EROTC QLQ-C30 instrument.

*Feasibility and Acceptability measures:*

A. Patient/carer recruitment and retention rates:
  i. Number of identified eligible patients/carers at included hospital sites;
  ii. Number of consenting patients/carers at included hospital sites;
  iii. Number of participants reaching study completion at included hospital sites.
B. Acceptability of STEP Care intervention to patients/carers:
  i. Number of withdrawals from STEP Care intervention;
  ii. Number of adverse events arising from STEP Care intervention;
  iii. Qualitative interviews with STEP Care family carers following bereavement*.
C. Acceptability of STEP Care intervention to participating physicians:
  i. NAT: PD-C documentation completion rate by participating STEP care physicians;
  ii. Focus group with STEP Care physicians regarding perspectives on STEP care content, timing and frequency of interaction.
D. Refinement of STEP Care intervention procedures ensuring future replication:
  i. Percentage of initial STEP Care interactions occurring within planned 14 day timeframe;
  ii. Median total number of STEP Care interactions per patient/carer.
E. Refinement of outcome measures and data collection methods;
  i. To determine an estimate of effect size for potential patient- and carer- reported outcome measures and variance to inform power calculations for planned phase 3 trial.
  ii. Percentage of missing data on patient- and carer- reported outcome measures, i.e. acceptability of selected measures.
F. STEP Care intervention fidelity;
  i. Timing of intervention delivery: median number of days from enrolment to first STEP Care interaction, and subsequent STEP Care interactions.
  ii. Content of intervention: audit of random sample of 20% of audio-recorded consultations and associated documentation using the NAT: PD-C. [39]

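### Table 4's content-fidelity measure checks the notes against the recording, not the consultation against the Table 2 components, and the general practitioner case conference has no delivery measure

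*Protocol article*

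**What the plan says.** Table 2 (Methods, Intervention) sets out what STEP Care is. It lists eight domains, 2(a) to 2(h), under the initial consultation, then monthly follow-up for at least 3 months, then item 4: "4. Case conference with the general practitioner within 28 days, addressing" three topics.

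The Intervention section says of the record: "Those areas covered in each consultation will be recorded in a standardised manner using the framework provided by the PC-NAT-PD". Of the audio it says: "All STEP consultations will be audio-recorded to enable content review of services delivered". It then provides for "An audit of 20% of all audio-recorded consultations and associated documentation using the Needs Assessment Tool: Progressive Disease–Cancer (NAT: PD-C").

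Table 4 (Data collection) turns this into a measure. Its name is "Fidelity of step delivery between recording and documented activities using NAT:PD-C" and its unit is "Percentage content correlation within random audit of 20% of consultations". Item F.ii of the Appendix (Feasibility and Acceptability measures) lists the same audit as the content part of intervention fidelity. It names the tool but neither a content standard nor a scoring rule.

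On who delivers the care, the Intervention section says: "All STEP Care consultations will be conducted by an accredited palliative care physician or specialist nurse". The completion measure, in Table 4 and in Appendix item C.i, reads: "NAT: PD-C documentation completion rate by participating STEP care physicians".

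**The concern.** Fidelity of a complex intervention is a comparison of what was delivered with what was specified. The Table 4 measure compares what was recorded on audio with what was written down. It is carried out on the right material, but it answers a different question.

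This matters because the trial's premise is standardisation, and its results are meant to refine the model and support replication in phase 3. A high agreement figure reported under the name of fidelity could be read as evidence that a standard package was delivered. Content could differ between sites or between clinicians without moving that figure, as long as the notes were honest. A quality-of-life signal in either direction would then be harder to attribute to STEP Care as Table 2 defines it.

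The case conference is a second gap. It is a numbered key component with a time limit, it takes place outside the audited consultations, and none of the listed measures counts it.

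**Working it through.** The article gives no fidelity value, target or formula, so there is no figure to reproduce. The check is a worked example on the eight consultation domains of Table 2, with each domain marked as delivered or not (heard on the recording) and documented or not.

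**Inputs.** K = 8 domains, Table 2 items 2(a) to 2(h). The numbers delivered and documented are illustrative.

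**Formulas.**
- Delivery = domains delivered / 8.
- Because the unit in Table 4 is not defined further, agreement was computed in four ways: (i) domains on which recording and notes agree / 8; (ii) documented domains that are heard / documented domains; (iii) heard domains that are documented / heard domains; (iv) domains both heard and documented / domains heard or documented.

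**Results.**

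| Delivered | Documented | (i) | (ii) | (iii) | (iv) | Delivery |
|---|---|---|---|---|---|---|
| 3 | the same 3 | 100% | 100% | 100% | 100% | 3/8 = 37.5% |
| 8 | 8 | 100% | 100% | 100% | 100% | 8/8 = 100% |
| 8 | 4 of them | 4/8 = 50% | 4/4 = 100% | 4/8 = 50% | 4/8 = 50% | 8/8 = 100% |
| 2 | 8 | 2/8 = 25% | 2/8 = 25% | 2/2 = 100% | 2/8 = 25% | 2/8 = 25% |

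Rows 1 and 2 cannot be told apart under any of the four versions. Row 3 shows the opposite error: full delivery with thin notes looks poor under three of the four. Row 4 shows what the measure can detect under three of the four, which is over-documentation.

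**Coverage of the other Table 2 components.**
- Monthly follow-up: covered. Table 4 and Appendix D.ii count contacts per patient, and Appendix F.i gives the time to the first and later contacts.
- First consultation on time: covered by the 14-day percentage.
- Case conference: no entry in Table 4 or in Appendix items A to F. The nurse-led diary prompts for general practitioner visits, but those are the patient's service use, not a conference between clinicians.

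**Size of the audit.** With 90 patients at 1:1 there are 45 in the STEP arm, and at the minimum of four consultations 45 × 4 × 0.20 = 36 recordings. The 30 per group stated in Planned analyses gives 30 × 4 × 0.20 = 24. Both are before attrition, and neither bears on the point.

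**The case against.** The strongest reply is that the article does describe an audit of content. The recordings are made for content review, Appendix F.ii is headed as content, and the NAT: PD-C is a structured tool whose domains may overlap with Table 2. Audit scoring sheets are also commonly left to a full protocol. This stands in part: the audit data could support delivery scoring, and the unit in Table 4 is loosely worded. But Table 4 does not leave the measure open. It names the two things compared, and Table 2 is not one of them; nothing in the article maps the tool to Table 2.

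A second reply is that the completion rate, the share of content recorded per consultation, would fall in the 3-of-8 example and so expose it. On one reading it would, to 3/8 = 37.5%. But it is filed under acceptability to clinicians, rests on the deliverer's own record, and does not say how a domain marked as not covered is counted. It offsets the gap partly.

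Three stronger readings are tempting, and the documents do not support them:
- That delivery as a whole goes unmeasured. Number and timing of visits are measured; the gap is content and the case conference.
- That nurse-run visits drop out of fidelity. The audit draws on all recorded consultations, so they are included. The physician-only wording affects the completion measure. It also appears in the Table 4 focus-group entry, but the Qualitative data collection section describes focus groups with health professionals generally.
- That a known share of visits is lost to the completion measure. The article gives no figure for nurse-run consultations.

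**Conclusion.** The point holds as a matter of definition. The content-fidelity measure in Table 4 is documentation accuracy under another name, and it can err in both directions: 100% agreement with 37.5% delivery, or 50% item agreement with 100% delivery. These are illustrations of what the measure permits, not forecasts of what the trial will find. They rest on treating the eight Table 2 items as the content standard and on scoring domain by domain. The first holds under all four versions of agreement tried, the second under three of them. The case conference has no delivery measure.

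The consequence is limited. The measure is descriptive and has no threshold, and the primary feasibility endpoint (90 enrolled across three sites in 24 months, at least 60% reaching 12 weeks) does not use it. What is at stake is how far phase 3 can rely on the reported fidelity.

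**What to change.** 1. In the same 20% audit, score recordings of initial consultations against Table 2 items 2(a) to 2(h), and report the percentage of domains delivered as content fidelity.
2. Score follow-up recordings against whichever of those domains the protocol states apply at follow-up. Table 2 ties the eight items to the initial consultation, while the Intervention text refers to a series of domains at each one. The investigators need to reconcile the two first; otherwise a follow-up visit that conforms to Table 2 could score as low fidelity.
3. Keep agreement between recording and notes, and report it separately as documentation accuracy.
4. Add the percentage of STEP patients with a general practitioner case conference held within the 28 days that Table 2 states.
5. Align the wording of the completion measure in Table 4 and Appendix C.i with the Intervention section, so that it covers physicians and specialist nurses.

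The recordings and the sampling fraction stay the same. The cost is a slightly longer audit sheet, one added count, and a fidelity figure likely to be lower than the agreement figure.

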### Qualitative data collection

Qualitative focus groups will be conducted with health professionals at the study sites to explore the perceived impacts and benefits of STEP Care. In particular, the discussion will explore the views of the timing of STEP Care, the barriers and benefits of its implementation, content, frequency and minimum dose considered meaningful. These focus groups will be recorded, transcribed and analysed for impacts, benefits and additional content.

Interviews with a sample of approximately 15 bereaved family carers will be conducted. The aim of these interviews is to ascertain carers’ reflections associated with the provision of palliative care; specific feedback will be sought including their preferences for the timing of the introduction of palliative care. On their time three questionnaires, a question about willingness for follow-up interview will be listed with a yes/no response format and an open-ended space which request a phone number and best time to call. Of those who express willingness, one in three carers will be approached to invite continued willingness for interview either after the patient’s death or at completion of 3 months of data collection. Interviews following a semi-structured format may be conducted at the hospital or over the telephone and will be recorded and transcribed.

### Planned analyses

Feasibility and health utilisation outcomes will be summarised with descriptive statistics, including frequency counts and percentages (categorical variables) and mean/standard deviation or median/interquartile range (continuous variables) as appropriate.

Preliminary efficacy outcomes for patients (QOL, symptom impact, mood, performance status) and carers (QOL, mood, preparedness, care satisfaction) will be compared between treatment groups, after adjusting for baseline levels using analysis of covariance (ANCOVA). Separate ANCOVA models will be fitted for patients and carers. Results will be presented as estimates and 95% confidence intervals.

From our understanding of the sites, we estimate that the target sample size is *n* = 30 patients/carers per treatment group and *N* = 90 patients/carers overall total. This aligns to an anticipated achievable recruitment rate of approximately two patients/carers per month, per site, over 24 months. Ideally, the aim is for this total of 90 to be distributed equally by tumour type and site based on the minimisation protocol as part of the randomisation process.

A cost-utility analysis will be conducted whereby preference algorithms validated in an Australian population are applied to a cancer-specific, multi-attribute utility index (QLU-C10D) [40] calculated from patient-reported QOL scores (QLQ-C30) [41, 42]. Utility weights will be used to calculate quality-adjusted life years (QALYs). An incremental cost-effectiveness ratio (ICER)—additional costs incurred by intervention divided by any potential effectiveness gained from the intervention—will be calculated to determine cost ($) for each unit of outcome gained. ICERs will be referenced against established UK cost-per-QALY thresholds [43] set by the National Institute for Health and Care Excellence to determine ‘cost-value’ of medical interventions.

Qualitative analysis of interviews and focus groups with health care professionals will be undertaken using a thematic approach consistent with the goal of understanding feasibility, facilitators and barriers in provision of structured integrated palliative care. Interviews with bereaved family carers will be informed by a thematic framework, with flexibility to explore and understand new ideas as they emerge within the data.

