## Methods

### Primary aim

To determine the feasibility of conducting a definitive phase 3 randomised trial, which evaluates effectiveness of STEP Care (compared to usual best practice cancer care) for patients with advanced breast or prostate cancer or HGG. The specific feasibility endpoint is defined as enrolment of 90 patients across three sites in 24 months, with at least 60% of patients progressing to study completion, defined as 12 weeks post baseline. This will inform the planning of a subsequent phase 3 study including numbers of centres necessary to recruit the required sample size.

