#### Randomisation

Patient-level randomisation will be centralised and coordinated by the trial coordinator who, in real time, accesses the independent blinded system, separate to the treating clinical and patient-interfacing research staff. The randomisation schedule involved 1:1 allocation and used the minimisation method to ensure a balanced distribution between groups with respect to the patient’s tumour type and hospital site. After consent and baseline data is obtained, the research nurse telephones the trial coordinator for the outcome of the randomisation process. The research nurse will liaise with the treating clinician to inform them of the outcome of randomisation.

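### The efficacy ANCOVA adjusts for baseline only and leaves out tumour type and hospital site, the two factors on which allocation is minimised

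*Protocol article*

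**What the plan says.** Under Planned analyses, patient and carer efficacy outcomes are compared between arms "after adjusting for baseline levels using analysis of covariance (ANCOVA". The section adds "Separate ANCOVA models will be fitted for patients and carers" and "Results will be presented as estimates and 95% confidence intervals". It names no covariate other than baseline, no hypothesis test and no analysis visit.

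Under Randomisation, the allocation is 1:1 and "used the minimisation method to ensure a balanced distribution between groups with respect to" the patient's "tumour type and hospital site". Each factor has three levels: breast cancer, prostate cancer or high grade glioma, and three hospitals. Planned analyses mentions the minimisation again when it discusses how the 90 patients should be spread, but not as part of the model.

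The Primary aim counts the trial as feasible "with at least 60% of patients progressing to study completion, defined as" 12 weeks after baseline. Secondary aims, the Discussion and item E of the Appendix say that the quality-of-life effect, or effect sizes and variances more generally, will inform the phase 3 sample size.

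**The concern.** Minimisation removes most of the chance imbalance in tumour type and site, so these factors contribute little to the true variability of the arm difference. A model that omits them still counts their variance as error. The reported standard error is then too large, to the extent that the factors predict the outcome beyond the baseline score.

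The article gives some reason to expect this for tumour type. Its Background argues that prognosis, and hence the right time for referral, differs between cancers. Table 1 enrols the three tumour groups at different points in their illness.

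Two things are at stake: the precision of the efficacy intervals in a small trial, and the residual variance that is carried into phase 3 planning.

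**Working it through.** The article gives no interval width, standard deviation or effect size for these outcomes, so there is no figure of its own to reproduce. The check asks how much wider the baseline-only interval is than one that also adjusts for both factors.

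**Inputs from the article**
- Two arms, 1:1, minimised on two three-level factors (Randomisation).
- N = 90 (Primary aim, Planned analyses). Planned analyses also gives 30 per treatment group, which in two arms makes 60. That mismatch is a separate matter, and 90 is used here.
- 60% retention at 12 weeks (Primary aim): 0.6 × 90 = 54 patients.

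**Assumptions, not in the article**
- Correlation of 0.5 between baseline and outcome.
- R², the share of the variance left after baseline that the two factors explain: 0 to 0.30, split equally between them.
- Minimisation that favours the less-loaded arm with probability 0.8.
- Loss to follow-up at random and no true effect.

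**Approximate formula.** With good balance, the ratio of the baseline-only to the adjusted width is about 1/√(1 − R²). For R² = 0.10, 0.20 and 0.30 this gives 1.054, 1.118 and 1.195.

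**Simulation**, 4,000 trials per setting. The Monte Carlo standard error of a coverage figure is √(0.95 × 0.05 / 4,000) = 0.34 percentage points. Widths are in outcome SD units.

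| R² | Ratio, all 90 observed | Baseline-only width, 60% observed | Adjusted width, 60% observed | Ratio, 60% observed | Coverage, baseline-only, 60% observed | Coverage, adjusted, 60% observed |
|---|---|---|---|---|---|---|
| 0 | 0.998 | 0.956 | 0.976 | 0.98 | 95.5% | 95.3% |
| 0.05 | 1.02 | 0.956 | 0.951 | 1.01 | 95.9% | 95.3% |
| 0.10 | 1.05 | 0.957 | 0.927 | 1.03 | 96.0% | 94.7% |
| 0.20 | 1.12 | 0.959 | 0.876 | 1.10 | 96.3% | 95.2% |
| 0.30 | 1.20 | 0.962 | 0.819 | 1.17 | 96.7% | 95.3% |

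With all 90 observed, the simulated ratios match the formula. With about 54 observed they are a little lower, because the four extra coefficients cost relatively more (residual degrees of freedom 54 − 3 = 51 against 54 − 7 = 47) and loss to follow-up disturbs the balance. The mean treatment estimate was within 0.006 SD of zero under both models in every setting, so the omission causes no bias.

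**Phase 3 variance.** Sample size is proportional to residual variance. The baseline-only variance is 1/(1 − R²) times the adjusted one: 1/0.9 = 1.11, 1/0.8 = 1.25 and 1/0.7 = 1.43.

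**Repeated visits, checked separately.** These simulations used three post-baseline visits, about 60% retention at the last, correlation 0.5 or 0.7 and no true effect, with 1,500 trials per setting. The standard deviation of the 12-week estimate from ANCOVA on the observed values was 1.005 to 1.041 times that from a likelihood repeated-measures model. Using all visits therefore gains about 0.5% to 4%. ANCOVA bias was about 0 when dropout was unrelated to earlier scores, or related equally in both arms. It was −0.06 to −0.08 SD only when that relation was made to differ by arm.

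**The case against.** The strongest objection is that the size rests wholly on an assumed R². A baseline score on the same instrument may already absorb much of any tumour-type difference, and the article gives no reason why the patient's tumour type should predict carer outcomes. At R² of 0.05 to 0.10 the gain is 1% to 3%, and at zero adjustment costs slightly more than it returns. The intervals err on the safe side, no test or power is stated for these outcomes, and an inflated variance can only push phase 3 towards a larger trial. A fuller protocol or SAP may also name the two factors already. All of this stands, and it limits the point to a minor one. It does not remove it: the article states the model and its adjustment, and the balanced factors are not in it.

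Two stronger readings are tempting, and the document does not support either.
- A reader might infer that the estimates will rest on completers only. The article names no analysis visit, no restriction to completers and no missing-data method. Those details are commonly left to the full protocol or SAP. The bias shown above also needs dropout that depends on earlier scores differently by arm, a pattern that nothing in the article establishes.
- A reader might infer that ignoring the repeated visits makes the intervals too wide. The gain from using all visits is too small to carry that claim. A mixed model is also a debatable remedy here: the transition points were chosen because they herald a prognosis under six months, so much of the loss may be death, and such a model estimates scores as though those patients had continued.

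**Conclusion.** The point holds in a limited form. The efficacy ANCOVA omits both minimisation factors. If they are prognostic beyond baseline, the 95% intervals are valid but conservative: about 3%, 10% and 17% too wide at 60% retention for R² of 10%, 20% and 30%. Over the whole assumed range of 0 to 30%, the baseline-only interval is 0.98 to 1.17 times the adjusted width. The residual variance passed on is then too large for a phase 3 trial that adjusts for these factors.

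That the model and the allocation do not match is certain from the text; the size is conditional on the assumptions listed. Severity is minor. The primary endpoint is feasibility and is summarised descriptively, and efficacy is secondary and labelled preliminary. The link to phase 3 planning is what makes the correction worth having.

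**What to change.** In Planned analyses, add tumour type and hospital site as covariates, next to the baseline score, in the patient and carer ANCOVA models. Report the residual variance from the adjusted model for phase 3 planning. If the full protocol or SAP already lists the two factors, only the article's wording needs to be brought into line.

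The cost is a change of wording, since both factors are recorded at randomisation, and four degrees of freedom (two per three-level factor). If the factors explain nothing, that costs about 2% in interval width at 60% retention and almost nothing with all 90 observed.

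A repeated-measures model is optional. If used, it should be a sensitivity analysis with deaths reported by arm beside it.

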### Design

This study will involve a phase 2, multicenter, open-label, parallel-arm, randomised controlled trial (RCT) of STEP Care plus standard best practice cancer care versus standard best practice cancer care alone. This RCT has been designed within the Medical Research Council (MRC) framework for the development and testing of complex interventions [28, 31]. The MRC framework prioritises phased, sequential and intervention development leading towards implementation [28, 31]. Thus, this study is underpinned by the investigators’ earlier exploratory data resulting from qualitative [9, 26, 36, 37] and phase 1 modelling studies [15, 24, 34, 38] to define transition points where palliative care should, at minimum, be integrated. The transition points, defined by our previous work which will be used as the time of integration in this RCT, are presented in Table 1. Of note, these transition times are viewed as a minimum standard of care, with palliative care integration implemented if it has not already occurred. Consistent with the MRC framework, this phase 2 trial tests the feasibility of implementing palliative care at these transition points, before proceeding to a definitive phase 3 trial.

**Table 1 Tab1:** Transition point definitions

Prostate cancer	Presence of metastatic disease and multi-day hospital admission
Breast cancer	Presence of visceral metastatic disease (metastases involving organs other than bone only) and multi-day hospital admission
High grade glioma	Hospital presentation (inpatient or outpatient): first recurrence of primary HGG where pathological or clinical diagnosis is glioblastoma/WHO grade IV disease or first diagnosis of primary HGG and no cancer specific treatment being prescribed

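### Thirty per treatment group gives 60 patients in this two-arm, 1:1 trial, not the stated 90; the per-arm figure should be 45

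*Protocol article*

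**What the plan says.** The sample size appears in the protocol article under Planned analyses. One sentence gives both "30 patients/carers per treatment group and" and "90 patients/carers overall total". The sentence after next hopes to see the 90 "distributed equally by tumour type and site based on the minimisation protocol as part of the randomisation process".

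Three other sections bear on these figures:

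- **Design** describes a two-arm comparison: "STEP Care plus standard best practice cancer care versus standard best practice cancer care alone".
- **Randomisation** fixes the ratio: "The randomisation schedule involved 1:1 allocation", using minimisation to balance the groups on tumour type and hospital site.
- **Primary aim** defines the recruitment half of the feasibility endpoint as "enrolment of 90 patients across three sites in 24 months". The other half is that at least 60% of patients reach 12 weeks.

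**The concern.** In a two-arm trial with equal allocation, the total is twice the per-arm number. Here the stated total is three times the stated per-arm number. Thirty is what results from dividing 90 by three, and the trial has three tumour types and three sites, but neither of these is a treatment group.

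The minimisation sentence shows the same mixing of strata and arms. Minimisation acts after consent and baseline assessment, when a patient's tumour type and hospital are already fixed. It decides which arm the patient joins. How many patients of each type, or from each hospital, are enrolled depends on the consecutive recruitment described under Recruitment and consent.

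Two things are at stake. A reader who takes 30 per arm as the recruitment target would plan for 60 patients and miss the enrolment endpoint by a third. The per-arm number also tells readers how precise the between-arm quality-of-life estimate is expected to be, and the article intends to use that estimate to size a phase 3 trial.

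**Working it through.** **Inputs, all from the protocol article**

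| Input | Value | Section |
|---|---|---|
| Arms | 2 | Design |
| Allocation | 1:1 | Randomisation |
| Size per treatment group | 30 | Planned analyses |
| Overall total | 90 | Planned analyses; Primary aim |
| Tumour types, sites | 3 and 3 | Design (Table 1); Study setting |
| Completion threshold | at least 60% | Primary aim |

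**Step 1: try to reproduce the stated total.** N = arms × n per arm = 2 × 30 = 60. The stated 90 is not reproduced; the shortfall is 30, or 30/90 = 33%. Working back from the total, 90 / 2 = 45 per arm.

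**Step 2: look for a reading that reconciles 30 with 90.**

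- *Three groups:* 3 × 30 = 90, but the only threes in the design are tumour types and sites. Elsewhere in Planned analyses, outcomes are compared between treatment groups by ANCOVA, so the term there means the randomised arms.
- *Unequal allocation:* at 2:1, 90 splits into 60 and 30, but the ratio is fixed at 1:1.
- *Inflation for dropout:* 60 completers at 60% completion need 60 / 0.6 = 100 enrolled. The common shortcut gives 60 × 1.4 = 84. Neither is 90.
- *Thirty as completers per arm:* 0.6 × 90 = 54, or 27 per arm, not 30. Going from 90 to 60 needs a loss of 1 − 60/90 = 33.3%, which the article does not state.

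Only division by tumour type or by site returns 30. That this is where the 30 came from is an inference; the article does not say so.

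**Step 3: decide which figure is wrong.** Ninety appears in the Primary aim and twice in Planned analyses. Thirty per treatment group appears once. The per-arm figure is therefore the one to correct.

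**Step 4: effect on precision.** For an unadjusted comparison of two means with equal variances, the 95% confidence interval half-width in SD units is t(0.975, 2n − 2) × √(2/n).

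| Basis | n per arm | Half-width (SD) |
|---|---|---|
| 30 enrolled per arm | 30 | 0.517 |
| 45 enrolled per arm | 45 | 0.419 |
| 30 enrolled, 60% complete | 0.6 × 30 = 18 | 0.677 |
| 45 enrolled, 60% complete | 0.6 × 45 = 27 | 0.546 |

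The interval implied by 30 per arm is 0.517 / 0.419 = 1.23 times as wide as the one implied by 45. At 60% completion the ratio is 0.677 / 0.546 = 1.24.

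**The case against.** The best counter-argument concerns the consequence, not the arithmetic. Ninety is the operative number: it defines the endpoint and is repeated, while 30 appears once and no stopping rule is tied to a per-arm count. Recruitment would stop at 60 only if someone followed the per-arm figure. Precision will depend on the number actually analysed, and what passes to phase 3 is the estimated effect and variance, not the printed 30. No power calculation is overturned, because none is given and the primary aim is feasibility. All of this stands. It limits the practical harm, but it does not make the sentence correct.

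The half-widths are also open to qualification. They are unadjusted, whereas the plan uses baseline-adjusted ANCOVA, which narrows both intervals to the extent that baseline predicts outcome. The 60% figure is a minimum, so the last two rows of the precision table describe the threshold and not an expected rate. These points affect the absolute values, while the ratio between 30 and 45 per arm changes little.

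On minimisation, it is fair to say that the Randomisation section describes the method's role properly and that the Planned analyses sentence is worded as an ideal. That makes the slip minor. It still names minimisation as the means to an end it cannot deliver, and should be reworded.

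**Conclusion.** The point holds. Thirty per treatment group and 90 overall cannot both be true of a two-arm, 1:1 trial, and nothing in the article reconciles them. The discrepancy is 60 against 90 patients, or 30 against 45 per arm. In precision it is about 0.52 SD against 0.42 SD for the unadjusted 95% half-width, or 0.68 SD against 0.55 SD if only 60% complete in each arm.

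The choice of 45 as the correct per-arm figure rests on taking 90 as the intended total, which the primary endpoint supports. The half-widths assume equal variances and no baseline adjustment, and serve only to show the scale of the difference. The endpoint, total, allocation ratio and analysis method are unaffected.

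**What to change.** In Planned analyses, state the target as 45 patients per treatment group and 90 overall. If 30 was meant as a number per tumour type or per site, say so separately and label it an expectation, not a target.

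Replace the minimisation sentence with wording to this effect: minimisation balances the two arms within tumour type and hospital site; the totals by tumour type and site follow from consecutive enrolment.

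Any other document that cites 30 per arm should be corrected to match. The cost is a change of wording in two sentences, with no extra patients.
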